## Objectives {10}

This trial aims to evaluate the efficacy and safety of a plant-based dietary intervention for mitigating CIGT in patients with CRC receiving FOLFOX chemotherapy, compared with a conventional dietary intervention and a conventional dietary intervention supplemented with an Oncology Complete Nutritional Formula.

Primary objective: To compare changes in gastrointestinal symptom burden, serum inflammatory biomarkers, and gut microbiota composition and structure from baseline to week 6 among the three study groups.

Secondary objectives: To compare, from baseline to week 6, dietary intake and diet quality, emotional status, fatigue, nutritional status, and laboratory measures (blood counts and serum nutritional, metabolic, immunological indicators, and tumour markers) across groups.

Safety objective: To assess safety by comparing intervention-related adverse events (including food allergy, hypoglycaemia, and unintended weight loss) across groups.

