### Sample size {19}

Sample size was estimated using the Tests for Two Proportions module in PASS 2025 for the primary endpoint, defined as experiencing any prespecified CTCAE gastrointestinal toxicity of grade ≥ 2. Given two prespecified primary comparisons, a Bonferroni-adjusted two-sided α of 0.025 and 80% power were applied. Based on Souza et al. [24], the assumed proportions were 0.176 in the intervention group and 0.533 in the control group. Under these assumptions, 30 evaluable participants per group are required for each primary comparison. To account for an anticipated 20% loss to follow-up, this was rounded up to 38 participants per arm (total N = 114; 1:1:1).

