Microbiome and metabolomics outcomes will be analysed according to prespecified metrics. For metabolomics, multivariate structure will be explored using ordination, and feature-level differences over time will be tested using regression/mixed-effects frameworks with false discovery rate (FDR) control; pathway-level enrichment analyses will be reported as supportive. Community-level differences will be assessed using distance-based methods, and feature-level analyses will apply appropriate regression frameworks with FDR control for multiple testing. Harms events will be summarized by group (incidence, severity, seriousness, and relatedness) and compared using χ^2^/Fisher’s exact tests or regression models as appropriate; serious adverse events and events leading to intervention discontinuation will be described descriptively.

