### Who will be included in each analysis {27b}

The primary analysis will follow the intention-to-treat (ITT) principle, including all randomised participants and analysing them in the groups to which they were allocated, regardless of adherence or protocol deviations. A per-protocol sensitivity analysis will be conducted excluding participants with major protocol violations and/or not meeting prespecified adherence criteria. Safety analyses will include all participants who received any component of the assigned intervention/comparator.

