This protocol has several strengths. The three-arm design uses clinically relevant comparators that reflect real-world nutritional management during chemotherapy and allows separation of effects attributable to a structured dietary pattern from those related to nutritional supplementation alone. Stratified randomisation by site and sex improves balance for key prognostic factors, and repeated measurements across the intervention window support evaluation of symptom trajectories rather than reliance on a single endpoint. The integration of clinical endpoints with inflammatory biomarkers and stool-based profiling provides an opportunity to generate mechanistic hypotheses and to identify candidate signatures associated with symptom severity or response, while the use of prespecified analytical approaches (including appropriate control for multiple testing in high-dimensional data) supports transparent interpretation.

There are several limitations to consider. Although participant blinding will be attempted using coded programmes and role separation, it may not be fully maintained in food-based interventions due to recognisable differences in dietary content and delivery. The follow-up period is limited to six weeks and may not capture longer-term effects beyond the planned window. Multi-omics analyses are exploratory and high-dimensional; findings will require cautious interpretation and independent validation. Generalizability may also be constrained by eligibility criteria and recruitment from two hospitals in one region, which may under-represent older patients, those with severe malnutrition, or patients receiving alternative chemotherapy regimens.

If the intervention demonstrates clinically meaningful reductions in CIGT with acceptable safety, the results will support the use of a structured plant-based dietary strategy as an adjunct to standard supportive care during FOLFOX chemotherapy and inform scalable implementation pathways in routine oncology practice. Even if effects are modest, the trial will provide valuable feasibility information on adherence, retention, specimen completeness, and operational barriers that can guide refinement of dietary delivery models and the design of larger, longer-term confirmatory trials.

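### For uncommon harms, the named χ²/Fisher or unspecified regression comparison in arms of up to 38 says little about safety; risk differences with confidence intervals should be added (minor)

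*Protocol article*

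**What the plan says.** Protocol article, Objectives {10}, sets the safety objective: "To assess safety by comparing intervention-related adverse events (including food allergy, hypoglycaemia, and unintended weight loss) across groups".

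Statistical methods {27a} gives the analysis in one sentence with three parts. The first is descriptive: "Harms events will be summarized by group (incidence, severity, seriousness, and relatedness"). The second is comparative: "and compared using χ^2^/Fisher’s exact tests or regression models as appropriate". The third takes some events out of testing: "serious adverse events and events leading to intervention discontinuation will be described descriptively". No confidence interval, effect measure or significance level is named for harms.

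The safety set is defined in {27b}: "Safety analyses will include all participants who received any component of the assigned intervention/comparator". With the size fixed in Sample size {19}, "this was rounded up to 38 participants per arm (total N = 114; 1:1:1"), that is at most 38 per arm. That size was derived only for the gastrointestinal toxicity endpoint.

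The Discussion then makes its recommendation conditional: "If the intervention demonstrates clinically meaningful reductions in CIGT with acceptable safety, the results will support the use of a structured plant-based dietary strategy". Nothing in the document says how acceptable safety will be judged.

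**The concern.** The comparison that the protocol names and the purpose it serves fit poorly. A χ² or Fisher test asks whether the data rule out equal risk. A statement about acceptable safety needs the opposite information: how large an excess risk the data still allow. When a harm is uncommon and arms are small, a test will usually be non-significant even if the harm is two or three times as frequent on the plant-based diet, and the p-value does not show how much excess remains possible.

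At stake is how the results read. Food allergy, hypoglycaemia or weight loss could be reported as not significantly different between arms, beside a conclusion that depends on safety, without the reader seeing how weak that evidence is. Group incidences alone do not repair this, because they carry no measure of uncertainty.

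**Working it through.** **1. The plan's own size.** Inputs from Sample size {19}: proportions 0.176 and 0.533, "a Bonferroni-adjusted two-sided α of 0.025 and 80% power were applied", 20% loss. With unpooled variance:

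n = (2.2414 + 0.8416)² × (0.176×0.824 + 0.533×0.467) / 0.357² = 9.505 × 0.3939 / 0.1274 = 29.4, so 30 evaluable per group.

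30 / 0.80 = 37.5, so 38 per arm. The stated figures reproduce. They concern a 35.7-point difference in a common event and carry no information about harms.

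**2. Inputs for harms.** The safety set gives n = 38 per arm at most. The protocol states neither a harm rate nor an α for harms, so both are assumed here: two-sided 0.05 and several comparator rates.

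**3. Chance of a non-significant result.** For true risks p₁ and p₂, sum Bin(x; 38, p₁) × Bin(y; 38, p₂) over all pairs (x, y) whose two-sided p-value exceeds 0.05.

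| Comparator vs plant-based risk | Missed, uncorrected χ² | Missed, Fisher |
|---|---|---|
| 5% vs 10% | 86% | 96% |
| 5% vs 15% | 67% | 84% |
| 5% vs 20% | 45% | 62% |
| 10% vs 20% | 76% | 85% |
| 10% vs 30% | 39% | 50% |
| 15% vs 45% | 16% | 22% |

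If harms were tested at 0.025, the 5% vs 15% row would become 77% and 91%. About 141 per arm would be needed for 80% power in that row at 0.05 (normal approximation, pooled variance).

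**4. What an interval adds.** Suppose 6/38 (15.8%) on the plant-based diet against 2/38 (5.3%) on a comparator.
- Fisher p = 0.26; uncorrected χ² p = 0.13. Neither is significant.
- Wilson limits are 7.4% to 30.4% and 1.5% to 17.3%.
- Newcombe 95% limits for the difference of 10.5 points:
  - lower: 10.5 − √[(15.8−7.4)² + (17.3−5.3)²] ≈ −4 points
  - upper: 10.5 + √[(30.4−15.8)² + (5.3−1.5)²] ≈ +26 points

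The test reports no significant difference. The interval shows that an excess of about 26 points has not been ruled out.

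**5. No events in an arm.** The exact upper limit for 0/38 is 1 − 0.025^(1/38) = 9.3% (two-sided 95%), or 1 − 0.05^(1/38) = 7.6% (one-sided 95%).

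**The case against.** The strongest reply is that the protocol commits no error here. It never says that a non-significant harms test will be taken as safety. A reader might infer that from putting the {27a} sentence beside the Discussion, but the Discussion clause is conditional, names no test and sets no decision rule. That reading is not supported, and it is not claimed here.

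Nor is it right that significance tests are the only means of judging safety. The {27a} sentence begins with descriptive summaries and allows regression, which can give effect estimates with intervals. It leaves serious adverse events and discontinuations untested. Harms {17} asks for incidence and severity distributions and a safety monitor, and section {28a} adds an independent data monitoring committee. All of this stands. It does not supply what is missing: monitoring governs the conduct of the trial, not the final safety statement, and the regression models are unspecified.

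The protocol is also not clear on which harms are tested. The withdrawal criteria give hypoglycaemia, weight loss above 2 kg per week and food allergy as examples of serious adverse events, which {27a} only describes, while Objectives {10} says such harms are compared. On either reading, no interval is named.

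Two further points stand. Low power for harms is usual in a trial sized for efficacy. And the detailed interval method may be in the analysis plan, which is not shown. Both argue for minor severity.

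Finally, the miss rates depend on assumed inputs. At 5% vs 20%, uncorrected χ² misses 45%, so a fourfold excess would more likely than not be detected by that test. It would be wrong to say that any plausible harm goes unseen.

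**Conclusion.** The point holds as a minor improvement. For harms with a comparator rate near 5%, the named tests would probably be non-significant under a doubling (86–96%) or a tripling (67–84%), so a non-significant result would say little about safety. For more frequent harms the problem fades: a tripling from 10% is missed 39–50% of the time, and from 15% only 16–22%.

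These figures assume 38 per arm analysed, two-sided α of 0.05 and the comparator rates shown; only the 38 comes from the protocol. The conclusion does not depend on the exact rates. For a stated objective on which the final recommendation partly rests, an interval answers the question that is asked, and a test of equality does not.

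**What to change.** In {27a}, add to the harms sentence:
- For food allergy or intolerance, hypoglycaemia, clinically relevant weight loss, any grade ≥ 2 event and serious adverse events, report the risk difference of the plant-based arm against each comparator with a 95% confidence interval (Newcombe or exact).
- Where an arm has no events, report the exact upper confidence limit.
- State that non-significant harms comparisons will not be read as evidence of safety.

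If a margin for acceptable safety is wanted, the sponsor's clinicians should set it before unblinding; this review proposes none.

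The cost is wording only, with no new data or patients. Under section {5} the analysis plan is still to be finalised before database lock and unblinding, so there is time. The downside is that the safety statement will look less favourable, because the intervals will be wide and will show that only large excess risks can be ruled out.

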### Who will be included in each analysis {27b}

The primary analysis will follow the intention-to-treat (ITT) principle, including all randomised participants and analysing them in the groups to which they were allocated, regardless of adherence or protocol deviations. A per-protocol sensitivity analysis will be conducted excluding participants with major protocol violations and/or not meeting prespecified adherence criteria. Safety analyses will include all participants who received any component of the assigned intervention/comparator.

### How missing data will be handled in the analysis {27c}

Every effort will be made to minimise missing data through the retention procedures described above. For longitudinal outcomes, mixed-effects models using maximum likelihood estimation will be the primary approach and can accommodate missing outcome data under a missing-at-random assumption. If additional handling is required (e.g., substantial missingness in key secondary outcomes), multiple imputation will be applied using prespecified models incorporating baseline variables, stratification factors, and available outcome history; results will be compared with complete-case analyses as sensitivity checks. For microbiome/metabolomics features, no imputation will be performed for unavailable samples; analyses will be based on available specimens, with missingness patterns summarized and sensitivity analyses performed where appropriate.

### Methods for additional analyses (e.g. subgroup analyses) {27d}

Prespecified subgroup analyses will be exploratory and will assess potential effect modification by site and sex (stratification factors), and other clinically relevant baseline characteristics as prespecified in the SAP. Subgroup effects will be evaluated by adding interaction terms (e.g., group × subgroup and group × time × subgroup where relevant) within the primary modeling framework. Adjusted analyses (e.g., additionally controlling for baseline values and key covariates) will be prespecified and reported alongside unadjusted summaries.

### Interim analyses {28b}

No formal interim analysis for efficacy is planned. Safety data will be monitored continuously by the study team, and any concerns regarding unexpected or unacceptable intervention-related harms will be reviewed by the Principal Investigator, with escalation and reporting to the ethics committee as required. Decisions to pause or terminate the trial for safety reasons will be made by the Principal Investigator in accordance with IRB/ethics requirements.

### Protocol and statistical analysis plan {5}

This protocol will be publicly accessible through publication and trial registration records. The SAP will be finalized before database lock and before unblinding of the analytic dataset, approved by the study leadership, and made available as a supplementary file with the protocol/publication or upon reasonable request from the corresponding authors.

## Oversight and monitoring

### Composition of the coordinating centre and trial steering committee {3d}

Day-to-day trial delivery will be coordinated by a Trial Management Group (TMG) based at the central coordinating centre. The TMG will be responsible for overall trial operations, including site start-up and training, recruitment coordination, intervention delivery oversight, protocol adherence, data management coordination, safety reporting, and preparation of trial reports. The TMG will include the chief/principal investigator(s), a trial coordinator/manager, site investigators from each participating hospital, intervention delivery representatives, a data manager, and a statistician. The TMG will meet regularly (e.g., every 2–4 weeks) and additionally as required to address operational issues. Independent oversight will be provided by a Trial Steering Committee, which will review trial progress, protocol compliance, and participant safety at predefined intervals (e.g., every 6 months) and advise on any major trial decisions; the TSC will convene additional meetings if triggered by safety concerns or major protocol issues.

### Composition of the data monitoring committee, its role and reporting structure {28a}

An independent Data Monitoring Committee (DMC) will oversee participant safety and trial integrity. The DMC will comprise at least three members with relevant expertise (e.g., clinical oncology, nutrition/supportive care, and statistics) who are independent of the sponsor/funder and the study investigators, with no competing interests. The DMC will periodically review accumulating safety data and key trial conduct indicators (e.g., recruitment, retention, protocol deviations) and may request unblinded summaries if necessary for safety evaluation. The DMC will provide written recommendations to the Trial Steering Committee/Chief Investigator regarding continuation, modification, temporary suspension, or early termination of the trial on safety grounds. Any serious safety concerns will be escalated promptly according to the reporting pathway defined in the DMC charter (available from the coordinating centre upon request).

### Frequency and plans for auditing trial conduct {29}

Trial conduct will be monitored using a risk-based approach aligned with Good Clinical Practice. Monitoring activities will include central checks of data completeness/consistency, verification of key documents (e.g., informed consent, eligibility), and review of adverse event reporting. On-site or remote monitoring visits may be conducted periodically (e.g., at least annually per site or more frequently if risk triggers arise), focusing on critical processes such as consent procedures, adherence to eligibility criteria, protocol compliance, source data verification for primary outcomes and serious adverse events, and data security practices. Audit findings will be documented, corrective actions will be agreed with the site team, and follow-up will be performed to ensure resolution.

### Protocol amendments {31}

Any important protocol modifications (e.g., changes to eligibility criteria, intervention procedures, outcomes, or analyses) will be documented as formal protocol amendments. Amendments will be submitted by the coordinating centre to the relevant ethics committees for approval prior to implementation, except where immediate changes are required to eliminate an urgent hazard to participants. Approved amendments will be communicated to all participating sites with updated study documents and, where necessary, retraining of site staff. Trial registry records will be updated in a timely manner. Participants will be informed of changes that may affect their willingness to continue participation, and re-consent will be obtained when required.

## Dissemination policy {8}

Trial results will be disseminated irrespective of the direction or magnitude of findings. The trial registration record will be updated and summary results will be reported in the registry in accordance with registry requirements. Findings will be submitted to peer-reviewed journals and presented at national/international conferences for healthcare professionals and researchers. Participants who wish to receive study results will be provided with a plain-language summary after completion of the primary analyses (e.g., via WeChat/telephone or routine follow-up contact), and a lay summary may be posted through institutional communication channels. All dissemination will present aggregated results only, without any participant-identifiable information, and authorship will follow International Committee of Medical Journal Editors (ICMJE) criteria.

## Discussion

This multicentre, stratified, three-arm randomised controlled trial is designed to evaluate the efficacy and safety of a structured plant-based dietary strategy for mitigating CIGT during FOLFOX chemotherapy in patients with CRC, compared with conventional dietary guidance with or without an oncology nutritional formula. In addition to repeated clinical assessments of gastrointestinal toxicity, the trial will collect inflammatory biomarkers and stool-based multi-omics data to support exploratory investigation of biological correlates of symptom burden and treatment tolerance.

Several practical and operational issues are important in executing this study. First, blinding is inherently challenging in food-based interventions. Differences in dietary content and intervention delivery may influence participant expectations and behaviour, and cross-group contamination is possible, particularly when patients seek additional dietary advice or modify intake in response to symptoms. To reduce these risks, the protocol emphasizes standardised intervention materials and contact schedules, separation of trial roles, and blinded outcome assessment wherever feasible. Second, maintaining dietary adherence during active chemotherapy is difficult, especially across transitions between inpatient chemotherapy delivery and the home-based interval. Treatment-related nausea, anorexia, oral mucositis, taste changes, and diarrhoea may lead to symptom-driven deviations from the assigned diet [6, 7]. The protocol addresses this by combining structured education with ongoing follow-up support and by quantifying adherence and dietary exposure using prespecified dietary instruments (FFQ, diet records, and plant-based diet indices), enabling interpretation of adherence and potential dose–response relationships. Third, concomitant medications and intercurrent events can substantially affect both gastrointestinal outcomes and gut microbial profiles. Antiemetics, antidiarrheals, corticosteroids, and especially antibiotics or probiotics may modify symptoms and microbiome composition [27, 28]. The protocol therefore includes prespecified restrictions for selected agents where appropriate, systematic documentation of concomitant treatments, and integration of these factors into analysis and interpretation. Lastly, the reliability of stool-based multi-omics findings depends on strict control of pre-analytical variation [29]. Harmonized SOPs for stool collection, time stamping, storage, and batch processing across sites are intended to minimise avoidable variability and improve reproducibility of downstream analyses.

This protocol has several strengths. The three-arm design uses clinically relevant comparators that reflect real-world nutritional management during chemotherapy and allows separation of effects attributable to a structured dietary pattern from those related to nutritional supplementation alone. Stratified randomisation by site and sex improves balance for key prognostic factors, and repeated measurements across the intervention window support evaluation of symptom trajectories rather than reliance on a single endpoint. The integration of clinical endpoints with inflammatory biomarkers and stool-based profiling provides an opportunity to generate mechanistic hypotheses and to identify candidate signatures associated with symptom severity or response, while the use of prespecified analytical approaches (including appropriate control for multiple testing in high-dimensional data) supports transparent interpretation.

There are several limitations to consider. Although participant blinding will be attempted using coded programmes and role separation, it may not be fully maintained in food-based interventions due to recognisable differences in dietary content and delivery. The follow-up period is limited to six weeks and may not capture longer-term effects beyond the planned window. Multi-omics analyses are exploratory and high-dimensional; findings will require cautious interpretation and independent validation. Generalizability may also be constrained by eligibility criteria and recruitment from two hospitals in one region, which may under-represent older patients, those with severe malnutrition, or patients receiving alternative chemotherapy regimens.

If the intervention demonstrates clinically meaningful reductions in CIGT with acceptable safety, the results will support the use of a structured plant-based dietary strategy as an adjunct to standard supportive care during FOLFOX chemotherapy and inform scalable implementation pathways in routine oncology practice. Even if effects are modest, the trial will provide valuable feasibility information on adherence, retention, specimen completeness, and operational barriers that can guide refinement of dietary delivery models and the design of larger, longer-term confirmatory trials.

